### Data collection

Parents register in the diary (Form B) daily during the base line week, two intervention weeks, and 6 days after the last visit at the study CHC. The study nurse collects the diaries at the study visits. The diaries from the follow up week are sent to the project leader by mail.

At the first visit the nurse collects demographic data (Form C) and information about smoking, allergies, colic in the family, complications, and the mother’s intake of prescribed medication during the pregnancy and after the delivery. Information about the infants’ feeding, birth weight, when the excessive crying started, and use of probiotics, dimeticone, herbal treatment, etc. is also collected in Form C.

In Form D parents’ experiences of changes in the infants crying, stooling and sleep as well as their perception of if their infant has received acupuncture or not, and whether they have noted any side effects associated with acupuncture are reported.

The acupuncturist note in a Form E which of the points that was used, time for stimulation, possible crying and if so for how long.

One week after the fourth visit, and after the parents have sent in the diary for the last week parents are phoned and asked the questions in Form D once more. Parents also report eventual treatments or medication provided by the CHC or by other therapists parallel to the study participation (Form F). Thereafter the parents are told their infant’s study allocation.

When each of the instruments is used in the trial is described in Table 1.

**Table 1 Tab1:** Telephone contacts, visits and instruments

	Baseline week for selection of infants fulfilling the criteria for colic		Intervention week 1		Intervention week 2		Follow up	
Telephone	Form A	Form A						Form F
Parents daily registration in a diary	Form B	Form B	Form B	Form B	Form B	Form B	Form B	
Visits to the study center.			X	X	X	X		
Study nurse collects informed consent			Form H					
Study nurse collects baseline data			Form C					
Study nurse collects data				Form D	Form D	Form D		
Acupuncturist registers treatment			Form E	Form E	Form E	Form E		

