**Methods/design:**

a multicenter randomized controlled three-armed trial for infantile colic conducted in four regions of Sweden. Alongside the standard program at their regular Child Health Center infants visit a study center twice a week for 2 weeks. The infants are randomly allocated into three groups.

According to the power analysis, 144 otherwise healthy infants aged 2–9 weeks old, who – according to parents’ registration in a diary – are crying and/or fussing more than three hours per day, more than 3 days per week will be included. Parents register daily in the diary during the baseline week, two intervention weeks, and one more week directly after the last study visit.

At four study visits at the Child Health Center parents meet a nurse for 20–30 min to receive advice and support. The nurse and the parents are blinded for group allocation. Infants are carried to another room, where they spend five minutes with an acupuncturist. Infants randomized to group A receive standardized minimal acupuncture in LI4. Group B receive individualized acupuncture where, according to symptoms, the acupuncturist can choose between the points Sifeng, LI4, and ST36. Group C receives no acupuncture.

The primary outcome is relative difference in crying, counted in minutes. Secondary outcomes are number of infants fulfilling the criteria for colic, and changes in sleep and stooling frequency. Adverse events and blinding are recorded.

Recruitment started in January 2013. During the first 14 months 93 patients were included. Data collection continues until May 2015. No interim analyses have been conducted.

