**Discussion:**

The study will provide information about the efficacy and safety of acupuncture as a complement to usual care in infants with colic.

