### Interventions

Parallel to usual care, study participants visited a study CHC where the intervention was conducted twice a week for 2 weeks. Parents met a nurse for 20–30 min. Parents described their situation, discussed the infant’s symptoms, and got evidence based support and advice. All parents received the information that having a baby with colic can be exhausting, and the nurse attempted to give them hope. The nurse informed parents about normal crying, that a healthy 6 week old infant cries an average of 1.5–2.5 h per day and that colic does not negatively affect the child’s development. Breastfeeding mothers were encouraged to continue to do so.

At each of the four study visits, the study nurse brought the infant to a separate treatment room where another nurse, trained in acupuncture, was alone with the infant for approximately five minutes. The acupuncture nurse treated the baby according to allocation and recorded treatment provided, as well as whether the baby cried and, if so, for how long. Adverse events and how they were dealt with was also recorded (Form E). After five minutes, the acupuncturist called the study nurse, who then carried the baby back to the parents.Group A:Infants received standardized minimal acupuncture in LI4. One needle was inserted approximately 3 mm deep in the point LI4 on the infant’s hand unilaterally for 2–5 s and then withdrawn.Group B:Infants received individualized acupuncture and the needles could be retained longer. A guideline for the choice of points was developed based on a previous practitioner survey conducted with experienced acupuncturists specialized in pediatrics [4]. It allowed acupuncturists to choose any combination of the acupuncture points Sifeng, LI4, and ST36, based on the symptoms reported in the diary. Maximum 5 needles were inserted approximately 3 mm. The point Sifeng was considered as four insertions, needled about one second each. Needles in LI4 and ST36 were retained for maximum 30 s each.Group C:Infants spent five minutes with the acupuncturist in the treatment room. The nurse held the infant’s hand and spoke to him/her in a calm voice.

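### As described, Form D asks blinded parents only about side effects they link to acupuncture, so adverse events after a visit are likely to be under-counted, and unequally so if allocation guesses differ by arm

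*Protocol article*

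**What the plan says.** Safety is a declared product of the trial: the Abstract's Discussion promises "information about the efficacy and safety of acupuncture". The Outcome measurement section says that adverse events will be reported. It attaches no hypothesis or test to them.

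Two sources of adverse event data are described.

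- **In the treatment room.** The Interventions section says of the acupuncture nurse's record: "Adverse events and how they were dealt with was also recorded (Form E". This covers the roughly five minutes in which that nurse is alone with the infant. The Blinding section says that the acupuncturist knows the allocation.
- **After the visit.** The Data collection section describes the parents' form. It begins "In Form D parents’ experiences of changes in the infants crying, stooling and sleep", goes on to "their perception of if their infant has received acupuncture or not", and ends with "whether they have noted any side effects associated with acupuncture are reported".

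Table 1 places Form D at the second, third and fourth visits. One week after the fourth visit, "parents are phoned and asked the questions in Form D once more". Parents do not know the arm at any of these times. The Abstract states "The nurse and the parents are blinded for group allocation", and the disclosure comes last: "Thereafter the parents are told their infant’s study allocation".

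**The concern.** A question about effects of acupuncture, put to someone who does not know whether acupuncture was given, takes in two things at once: whether something happened to the infant, and whether the parent believes that the infant was needled. A parent who believes that the infant was in group C has, on the item's own terms, nothing to report, whatever was seen at home. A group C parent who believes the opposite may report an ordinary symptom as a side effect.

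At stake is what the untreated arm can offer on safety. Group C could show how often such symptoms occur without needling, but only if the same question, free of attribution, is put to all three arms.

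**Working it through.** **Step 1: does another described form close the gap?**

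| Source | Completed by | Covers the time after a visit? | Free of attribution? | Content |
|---|---|---|---|---|
| Form E (Interventions) | Acupuncture nurse, unblinded | No, about five minutes in the room | Yes | Adverse events, treatment given, crying |
| Diary, Form B (Participant enrollment, Data collection) | Parents, daily | Yes, to 6 days after the last visit | Yes | Crying and fussing, sleep, feeding, stooling; no adverse event item listed |
| Form D, change items | Parents | Yes | Yes | Crying, stooling, sleep |
| Form D, side-effect item | Parents | Yes | **No** | Side effects linked to acupuncture |
| Form F (Data collection) | Parents, by telephone | Yes | Yes | Parallel treatments and medication |

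Events that show up as crying, sleep, feeding or stooling are captured in all arms without attribution. An event that led to treatment may leave a trace on Form F. For anything else, such as a local skin reaction, the only item that asks about it after a visit is the attribution-dependent one.

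**Step 2: what would the wording do to the counts?**

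The article gives no adverse event rate, no guess rate and no safety power, so there is no stated figure to reproduce. Every rate below is assumed, to show the mechanism.

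Let p be the true rate of after-visit events in an arm and g the share of its parents who believe that acupuncture was given. If only believers report, and all of them do:

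- reported rate = p × g
- share of events lost = 1 − g
- reported risk ratio = (pA × gA) / (pC × gC)

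Here A stands for a needled arm and C for the un-needled arm.

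Equal true rates, pA = pC = 10% (true ratio 1.00, true difference 0):

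| gA | gC | Reported A | Reported C | Ratio | Difference |
|---|---|---|---|---|---|
| 0.5 | 0.5 | 5% | 5% | 1.00 | 0 |
| 0.6 | 0.4 | 6% | 4% | 1.50 | 2 points |
| 0.7 | 0.4 | 7% | 4% | 1.75 | 3 points |
| 0.8 | 0.3 | 8% | 3% | 2.67 | 5 points |

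True rates of 15% v 10% (true ratio 1.50, true difference 5 points):

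| gA | gC | Reported A | Reported C | Ratio | Difference |
|---|---|---|---|---|---|
| 0.5 | 0.5 | 7.5% | 5% | 1.50 | 2.5 points |
| 0.6 | 0.4 | 9% | 4% | 2.25 | 5 points |
| 0.7 | 0.4 | 10.5% | 4% | 2.62 | 6.5 points |

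Two separate effects appear:

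1. **Under-counting** occurs whenever g is below 1, even if blinding works perfectly. Over the values used, the share lost runs from 1 − 0.8 = 20% to 1 − 0.3 = 70%. With equal guesses the ratio survives and the difference shrinks.
2. **Distortion between arms** needs unequal guesses. It can go either way: reversing the second row of the first table gives 4% v 6%, a ratio of 4/6 = 0.67.

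The all-or-nothing reporting rule is the extreme case. If parents who believe that no needling took place still report some share of events, the result lies between these figures and the true ones.

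**Step 3: the same model with a neutral item.** Reporting no longer depends on belief, so gA = gC = 1. The reported rates equal the true ones: 10% v 10% (ratio 1.00), or 15% v 10% (ratio 1.50, difference 5 points).

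**The case against.** A reader might infer that the safety comparison between arms is biased. The document does not support that, for three reasons.

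- No between-arm safety analysis is stated. The Statistical analysis section compares groups on crying and on the colic criteria, and adverse events are only to be reported.
- Bias in a ratio does not follow from the wording alone. With equal guesses the ratio is unchanged. Distortion needs guesses that differ by arm, or events such as needle marks that themselves prompt the guess. The article gives no figure for either.
- That parents infer the allocation from reduced crying is plausible, but the document does not show it.

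A reader might also infer that nothing after the visit is captured except through this item. That is too strong: the diary, the Form D change items and Form F all reach past the visit, and parents discuss the infant's symptoms with a blinded nurse at each of the four visits. These sources narrow the gap but do not close it, because none is described as soliciting adverse events.

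Two further objections carry weight. First, the article paraphrases Form D in one sentence. The form's exact wording and the order of its items are not shown, so the phrase may be shorthand for a broader question. This stands, and it makes checking the form the first step. Second, the guess is recorded on the same form and blinding will be reported, so dependence on belief can be examined with planned data. This also stands, but such a tabulation cannot recover events that no parent reported.

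**Conclusion.** The point holds in limited form. As the article describes it, the after-visit side-effect item depends on parents' attribution and hence on their guess. Events outside crying, sleep, feeding and stooling are therefore likely to be under-counted, and differentially between arms if guesses differ by arm. The document gives no basis for a size: the figures above rest on assumed event rates, assumed belief shares and an all-or-nothing reporting rule.

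The conclusion also assumes that the real Form D matches its description. The primary outcome is untouched. What is limited is the trial's stated contribution on safety, and the remedy is a cheap improvement while data are still being collected.

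**What to change.** 1. Check the actual wording and item order of Form D. If it already asks neutrally, correct the description and stop there.
2. If it matches the description, ask the parents of all remaining infants, in all three arms and in the same words, about any new symptom or health problem since the last visit. Place this before the allocation-guess item, use it also in the closing telephone call, and report events by arm.
3. For infants already assessed, tabulate the existing answers by arm and by parental guess. Label them parent-attributed side effects, not adverse events.

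The cost is one line on an existing form, plus the need to report the two wordings separately, because they are not comparable. The gain falls only on infants not yet assessed. At the 14-month count of 93 infants, that left 144 − 93 = 51 against the Abstract's target, or 192 − 93 = 99 against the Sample size section's figure. Fewer will remain by the time a change takes effect, so the check should be made promptly. The tabulation in step 3 needs no new data and is worth doing in any case.

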#### Statistical analysis

Statistical analyzes will be made from the data collected in forms and records (see Table 1), and carried out following a structured data management plan and by using appropriate statistical methods (dependent upon type and variable) for descriptive data as well as multivariate analysis.

We will analyze usual care plus standardized minimal acupuncture (group A) and individualized acupuncture (group B) versus usual care plus four extra visits to a CHC (group C). The mean difference over time and between groups in reduction in % of colicky crying, crying and fussing in minutes/day will be compared using relevant statistical methods depending on distribution.

We will use analysis of covariance at the baseline week, the first intervention week, the second intervention week and the week after the last visit to the study center to assess whether clinical differences, if any, are significant.

How many infants in each group who still cries and/or fusses more than three hours/day more than 3 days per week, i.e. fulfills the criteria for colic, each intervention week will be assessed by the difference in survival curves (days to crying <3 h/day) using Kaplan–Meier analysis.

Additional descriptive measurements will be presented on back ground data, the acupuncturists’ choice of points for group B, results on separate study centers and on blinding.

All data in this trial will be assessed by SPSS v22.0 (SPSS, Chicago, IL, USA). P <0.05 will be considered statistically significant.

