### Participants

Otherwise healthy infants not more than 8 weeks at registration and not more than 9 weeks when the intervention begins.

Inclusion criteria: infants who, according to parents’ record in the diary, cry and/or fuss more than three hours per day, more than 3 days per week were included and randomized. Infants should have tried a diet excluding cow’s milk protein for at least 5 days.

Exclusion criteria: being born before week 37, not gaining weight properly, having tried acupuncture, or taking any kind of medication (apart from dimeticone or lactobacillus reuteri).

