### Sample size

ACU-COL was designed to compare the effect of two types of acupuncture and no acupuncture in infants with colic. According to the power analysis, conducted by an independent statistician at the center for clinical research and development (R&D, Region Skane) and based on the results in an earlier trial with the primary outcome crying [7], 192 infants will be needed to detect a statistically significant difference between the two acupuncture groups assuming that a clinically relevant difference in crying per day between group A and group B is 30 min which is 11 % in relative difference between the first and the second intervention week compared to the baseline week.

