#### Outcome measurement

Primary outcome is relative difference in crying (mean values for the sum of fussing, crying and colicky crying) during the baseline week, during each of the two intervention weeks and during 6 days after the last treatment.

A secondary outcome is how many infants in each group who still cries and/or fusses more than three hours/day more than 3 days per week; i.e. fulfills the criteria for colic, each intervention week. Other secondary outcomes are change in frequency of stooling per day and change in hours of sleep per day during the same time frames. Adverse events, eventual parallel treatment or medication, how much infants cried from being needled and how well parents are blinded will be reported. Points chosen by the acupuncturists for infants in group B will be reported.

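### The weekly colic-status outcome is assigned a Kaplan–Meier analysis whose event an infant can reach while still meeting the colic criteria

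*Protocol article*

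**What the plan says.** The Outcome measurement section of the protocol article lists as a secondary outcome "how many infants in each group who still cries and/or fusses more than three hours/day more than 3 days per week". The time frame is given as "fulfills the criteria for colic, each intervention week". Each infant thus has one yes/no value for week 1 and one for week 2.

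The same threshold governs entry. Under Participants, infants who "cry and/or fuss more than three hours per day, more than 3 days per week were included and randomized". More than 3 days means at least 4 of 7.

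The Statistical analysis section restates the weekly outcome and then, in the same sentence, says it will be "assessed by the difference in survival curves (days to crying <3 h/day") by Kaplan–Meier. It does not say how many days below 3 h make an event, or whether the improvement must last.

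The data would support either analysis. The Data collection section says: "Parents register in the diary (Form B) daily during the base line week, two intervention weeks, and 6 days after the last visit".

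**The concern.** The outcome and its analysis answer different questions. The outcome asks how many infants have colic in a given week. The analysis asks how long it takes until crying falls below 3 h/day.

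The two differ in two ways. First, the colic criterion tolerates up to 3 days a week at or below 3 h, so a day below 3 h is compatible with colic in that same week. Second, colic status can reverse from week to week, whereas a Kaplan–Meier analysis of time to first event treats the event as final.

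At stake is the meaning of this secondary result. If the height of the curve at day 7 or day 14 is read as the share still with colic, infants who still have it are counted as resolved.

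**Working it through.** **Plan's own figure.** The article gives no number for this outcome or its Kaplan–Meier analysis, so there is nothing to reproduce. Its only computed design figure, the sample size, belongs to the primary outcome.

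**Step 1: logic, without assumptions about the data.** Take the event as written, on the daily diary, and set aside days of exactly 3 h.
- An infant above 3 h on 4, 5 or 6 of 7 days has colic that week and also has at least one day below 3 h. It has the event and the condition together.
- Only an infant above 3 h on all 7 days has colic that week without the event occurring in it.
- An infant without colic that week has at least 4 days not above 3 h, so it always has the event.

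Read as a measure of weekly resolution, the event can therefore only overstate it.

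**Step 2: the weekly-mean reading.** Suppose the parenthesis meant a weekly mean below 3 h/day. Four days at 3.1 h and three at 1 h give (4 × 3.1 + 3 × 1)/7 = 15.4/7 = 2.2 h/day. That infant meets the colic criterion with a mean below 3 h, so the mismatch remains.

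**Step 3: illustrative size.** Let p be the probability that a day is above 3 h. Assume independent days and no change in crying. Neither assumption comes from the article.
- Event by day t: 1 − p^t
- Weekly criterion met: P(X ≥ 4), with X ~ Binomial(7, p)
- Event in week 1 and criterion still met that week: P(X ≥ 4) − p^7

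At p = 4/7: p^7 = 0.020, so the event by day 7 has probability 1 − 0.020 = 0.980. The criterion is met with probability 0.653, and both hold with probability 0.653 − 0.020 = 0.633.

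| p | Event by day 3 | Event by day 7 | Criterion met in a week | Event in week 1 and criterion met |
|---|---|---|---|---|
| 4/7 | 81% | 98% | 65% | 63% |
| 5/7 | 64% | 91% | 89% | 80% |
| 6/7 | 37% | 66% | 99% | 65% |
| 0.95 | 14% | 30% | about 100% | 30% |

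At p = 6/7, for example, the curve at day 7 would stand at 34% event-free while 99% of such infants still meet the weekly criterion.

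**Step 4: sensitivity around the average the article implies.** The Sample size section says the relevant difference between "group A and group B is 30 min which is 11 % in relative difference". If the percentage refers to baseline crying, the mean is 30/0.11 = 273 min/day, or about 4.5 h. A simulation used this mean with normal variation, selection on the entry criterion, and no treatment effect or natural decline. The SDs were assumed: 45 to 90 min between infants and 45 to 90 min from day to day. Across these settings:
- 25–63% had the event by day 7
- 93–98% still met the criterion in week 1
- 21–58% had the event and still met the criterion in week 1
- 85–94% of infants with the event in week 1 still met the criterion that week

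**The case against.** The strongest defence is that the parenthesis is shorthand. It sits in a sentence whose subject is the full weekly criterion, it never says first day or single day, and a condensed article may leave the exact event to the full protocol or analysis plan. It is fair that a one-day event is an inference, though counting in days and the daily diary favour it. What does not stand is the idea that this is only missing detail: the article states a threshold and a method, and the threshold lacks the days-per-week part on either reading.

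Three stronger readings are tempting and are not supported.
- A reader might infer that most infants reach the event within days while still having colic. The article gives no daily crying distribution. In the table the joint figure for week 1 runs from 30% to 80%, and in the simulation it is below one half in most settings. The 98% is the chance of the event alone, for an infant at the entry boundary. Runs of similar days would lower the chance of an early day below 3 h.
- A reader might infer that the curves fall steeply in every arm and hide a real treatment difference. The first depends on the same unknown variation, and no power or bias calculation supports the second.
- A reader might see a further mismatch between crying in the event and crying or fussing in the criterion. Outcome measurement defines crying for the primary outcome as the sum of fussing, crying and colicky crying, which largely answers this.

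**Conclusion.** The point holds in a limited form. As written, the analysis does not estimate the stated outcome, because its event can occur while the weekly criterion is still met and takes no account of relapse. This follows from the definitions alone.

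The size is not known. The range of 30% to 98% with the event by day 7 rests on independent days, unchanged crying and assumed daily probabilities. The simulated 25–63% rests on assumed SDs around an inferred mean. One result is common to all simulated settings: most infants with the event in week 1 still had colic that week.

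This should be fixed, but it concerns one secondary outcome. The primary outcome, the sample size and the data collection are untouched.

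**What to change.** Classify each infant as colic yes or no in intervention week 1 and in intervention week 2, using the inclusion criterion. Compare the proportions between arms, for example as risk differences with 95% confidence intervals, or by logistic regression adjusted for the randomisation strata (age group and centre).

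If Kaplan–Meier is kept, list it as a separate outcome. Define the event as sustained loss of the weekly criterion, based on the sum of fussing, crying and colicky crying. State how the follow-up period is handled: it has 6 diary days, so a rule of more than 3 days is not the same test there as in a 7-day week.

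The cost is a change of wording in the analysis text. The diary already collects the daily data, and the article reports that no interim analyses have been conducted, so the change can be fixed before the outcome data are analysed.

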### Randomization

Infants were randomly allocated into one of three groups in proportions of 1:1:1, following randomization lists performed by an independent center for clinical research and development (R&D, Region Skane). The infants were randomized in two strata: infants aged 2–5 weeks and infants aged 6–9 weeks and therefore two randomization lists were created for each of the four centers. Infants were assigned to the three different treatments by sampling without replacement from a block consisting of, to the investigator, unknown number of labels from each treatment group. Researcher and clinicians had no influence on the allocation of infants.

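### The primary outcome has three post-baseline windows and no decisive window or group contrast under one flat 5% threshold, so its overall false-positive risk exceeds 5%

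*Protocol article*

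**What the plan says.** All references are to the Protocol article.

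- **Outcome measurement.** The primary outcome is the relative difference in crying, defined as the sum of fussing, crying and colicky crying. It is measured at baseline, "during each of the two intervention weeks and during 6 days after the last treatment". That makes three post-baseline windows, none ranked above the others.
- **Statistical analysis, timing.** The test is applied week by week: "We will use analysis of covariance at the baseline week, the first intervention week, the second intervention week", and then the week after the last visit.
- **Statistical analysis, groups.** The comparison is of "standardized minimal acupuncture (group A) and individualized acupuncture (group B) versus usual care plus four extra visits to a CHC (group C").
- **Statistical analysis, threshold.** One rule covers everything: "P <0.05 will be considered statistically significant".
- **Sample size.** The trial is sized on a different contrast: "192 infants will be needed to detect a statistically significant difference between the two acupuncture groups".
- **Background.** The first aim is to see whether earlier results with minimal acupuncture at LI4 can be repeated, which points to A versus C. The second aim compares both acupuncture types and no acupuncture, which involves all three groups.

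**The concern.** A primary outcome should lead to one decision. Here three windows and two or three group contrasts all qualify as primary, and the sections that could settle the choice disagree. The Sample size section points to A versus B, the Statistical analysis section to A and B versus C, and the aims to all three groups. The window is unsettled as well: the Sample size section mentions only the two intervention weeks, while the other two sections add the follow-up period.

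Under the stated rule, a significant difference in one week for one pair of groups could be reported as a positive primary result. The 5% level would then describe each test but not the trial's conclusion. This matters because the trial is meant to clarify an evidence base in which two earlier trials found an effect and one did not. A choice of window or contrast made after seeing the group results would not be convincing.

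**Working it through.** **The plan's own figure.** The article gives a per-test level of 0.05 and no overall error rate, so there is nothing to reproduce. The question is what overall rate the stated rule implies.

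**Inputs from the article**

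- Per-test level 0.05 (two-sided assumed; the article does not say).
- Three post-baseline windows. The baseline week is also listed for analysis of covariance but is not counted here.
- Two contrasts (A–C, B–C) from the Statistical analysis section, and a third (A–B) from the Sample size section.
- Equal arms: infants are "randomly allocated into one of three groups in proportions of 1:1:1".

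**Assumed inputs**

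- The correlation ρ between windows, taken as common to all pairs of windows and varied. The article gives no value.
- Any single significant primary test counts as a positive result.

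**Step 1: independent tests, for orientation.** The chance of at least one false positive among k independent tests is 1 − 0.95^k.

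- k = 3: 1 − 0.857 = 14.3%
- k = 6: 1 − 0.735 = 26.5%
- k = 9: 1 − 0.630 = 37.0%

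These overstate the risk, because the tests share arms and infants.

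**Step 2: correlation between contrasts.** With equal arms of size n and variance σ², each pairwise difference has variance 2σ²/n. Two contrasts that share an arm have covariance ±σ²/n, so their correlation is ±0.5. This follows from the design and needs no assumption about ρ.

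**Step 3: simulation under no effect.** Three equal arms, three windows, two-sided z-tests at 0.05, 400,000 replicates. The three-group test uses a chi-square statistic on 2 degrees of freedom, critical value 5.99. Chance of at least one significant result:

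| Reading of the plan, three windows | ρ = 0 | ρ = 0.5 | ρ = 0.7 | ρ = 0.9 |
|---|---|---|---|---|
| One three-group test per window | 14.4% | 12.6% | 11.2% | 8.5% |
| A–C and B–C pairwise | 24.9% | 21.9% | 19.3% | 14.9% |
| A–C, B–C and A–B pairwise | 32.5% | 28.5% | 25.0% | 19.5% |

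If only the two intervention weeks counted, the corresponding ranges for ρ from 0.5 to 0.9 would be 9.1–7.2%, 16.2–12.6% and 21.3–16.8%.

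**Step 4: naming a window is not enough by itself.** In one window, two ungated contrasts give 9.0% and three give 12.2%. One window with a global three-group test at 5%, followed by pairwise tests only if it is significant, gives 5.0%.

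**Step 5: what the global gate costs.** Assume a direct A–B test has 80% power, so its z-statistic is centred at 1.96 + 0.84 = 2.80. Requiring the global test to be significant as well gives about 76% power if group C has the same mean as one acupuncture group, and about 70% if C lies midway between them.

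**The case against.** **This may belong to an analysis plan that is not shown.** Test hierarchies and multiplicity adjustments are commonly left there, so their absence from a condensed article is no finding. That stands, and the point does not rest on it. It rests on what the article does fix: a multi-window primary outcome, sections that point to different contrasts, and one flat threshold.

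**The article does not prescribe pairwise tests.** Analysis of covariance on three groups naturally yields one group test per window. The Statistical analysis section also speaks of mean differences over time and of multivariate analysis, which could fit a joint analysis across weeks. This also stands. A reader might infer that the error rate simply is 20–29%, or that nine or more separate tests are laid down. The documents do not support either. The 20–29% range needs ungated pairwise testing of all three contrasts in all three windows, plus an assumed correlation.

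**The crying components.** Because the Statistical analysis section lists colicky crying, crying and fussing, a reader might count three endpoints. The Outcome measurement section defines their sum, so this reading is strained and adds nothing to the calculation.

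**The two sample sizes.** The abstract gives 144 infants and the Sample size section 192. That is a separate discrepancy. The error rates above do not depend on which number applies.

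**Conclusion.** The point holds, with a size that depends on the reading. The article gives the primary outcome three unranked post-baseline windows and no decisive contrast under a single 5% threshold. If any significant primary test counts as success, the overall false-positive chance exceeds 5% under every three-window reading examined.

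For an assumed between-window correlation of 0.5 to 0.9, it is about:

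- 9–13% with one three-group test per window
- 15–22% with A–C and B–C tested pairwise
- 20–29% with all three pairs

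The direction is certain under those readings. No single figure can be quoted as the trial's error rate, because the article fixes neither the reading nor the correlation.

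**What to change.** Before data are compared by group:

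1. **Name one primary window** for the summed outcome and make the others secondary. The mean over the two intervention weeks is one candidate. It should be stated as a choice, because the Sample size wording about those two weeks relative to baseline is ambiguous and does not define such a mean.
2. **Control the error across contrasts in that window**, by one of two routes:
   - a global three-group test at 5%, with pairwise tests at 5% only if it is significant. With exactly three arms this is a closed procedure, so no alpha needs to be split; or
   - one named primary contrast, or a fixed order of contrasts, each tested at 5% only if the one before it was significant.
3. **Align the Sample size and Statistical analysis sections** on the same contrast and window.

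**Cost.** Only analysis wording changes; design and data collection do not. Trial status reports that data collection is continuing and that no interim analyses have been done, so the choice can still be made credibly. A finding in a single week can no longer be claimed as primary. The global gate lowers A–B power from an assumed 80% to about 70–76%. A fixed order starting with A–B avoids that loss, but A–C and B–C can then be claimed only if A–B is significant.
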